**Methods:**

Regular smokers not intending to quit and without clinical signs of periodontitis will be randomly assigned (1:4 ratio) to either standard of care with brief cessation advice (control group; arm A) or C-F NA use (intervention group; arm B). The study will also include a reference group of never smokers (reference group; arm C). The primary end point is the change in the Modified Gingival Index (MGI) score from baseline between the control arm (arm A) and the intervention arm (arm B) at the 18-month follow-up. In addition, the study will analyze the within- and between-group (arms A, B, and C) changes in MGI assessment, plaque imaging, dental shade quantitation, tooth stain scores, and oral health–related quality of life questionnaires measured at each study time point. All participants will attend a total of 7 clinic visits: screening, enrollment, and randomization (visit 0); baseline visit—day 14 (visit 1); day 90 (visit 2); day 180 (visit 3); day 360 (visit 4); and day 540 (visit 5). This multicenter study will be conducted in 4 dental clinics in 4 countries. The statistical analysis will involve descriptive statistics for continuous and categorical data. Primary end points will undergo tests for normality and, based on distribution, either a 2-sided *t* test or Mann-Whitney *U* test. Linear mixed model with random factors center and study arms by center will also be applied. Secondary end points, including MGI assessment and quality of life, will be subjected to similar tests and comparisons. Only if one value of the parameter MGI is missing after day 1, the last available observation will be carried forward. The analysis will be performed on the substituted data. Secondary parameters will not have missing value replacement.

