**Figure 1 figure1:**
[figure not shown]
Study design. Smokers not intending to quit and without clinical signs of periodontitis were randomized to either standard care (arm A) or combustion-free nicotine alternatives (C-F NA; arm B). A reference group of never smokers will also be included but not randomized (arm C). Participants were prospectively reviewed at 4 dental clinics for cigarette consumption and C-F NA use, oral health and dental esthetic measurements, vital signs, and adverse events for up to 18 months.

The study flow is illustrated in Figure 2.

All participants will attend a total of 7 clinic visits: day −28 to day −1—screening; day 0—enrollment and randomization (visit 0); day 14—baseline visit (visit 1); day 90—week 12 (visit 2); day 180—week 24 (visit 3); day 360—week 52 (visit 4); day 540—week 76 (visit 5).

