**Figure 2 figure2:**
[figure not shown]
Study flow diagram of study participants. C-F NA: combustion-free nicotine alternatives.

Screening visits will be performed within 28 days before enrollment to verify the eligibility criteria (visit 0; Figure 2). During the screening visit, sociodemographic data, medical and oral health history, detailed information about nicotine and tobacco consumption, and interest in trying C-F NA will be recorded. Screening for periodontal disease will be performed to exclude periodontitis, as per the definition of the guidelines of the 2017 Classification of Periodontal and Peri-implant Diseases and Conditions [28]. Smokers will be offered a smoking cessation program as per local guidelines. Any smokers who express the intention of booking for the cessation program or to quit smoking in the next 6 months will be urged to do so and will not be recruited in the study. Participants taking part in the study will be informed that they are free to quit smoking and withdraw from the study at any time. Moreover, smokers will be encouraged to quit smoking at every contact throughout the study.

Within 28 days of the screening visit, eligible participants will be invited to attend an enrollment visit (visit 0). Inclusion and exclusion criteria will be verified again. Smokers will be reminded of the risks associated with smoking before enrollment in the study and that they are free to voluntarily quit smoking and nicotine or withdraw from the study at any time. All participants will undergo a series of measurements (Tables 1-3) followed by dental scaling and polishing procedures to remove calculus, plaque, and stain.

Smokers not intending to quit will then be randomly assigned to either the control (arm A) or the intervention (arm B) group. The randomization sequence will be generated by a computer, with an allocation ratio of 1:4 (arm A: arm B) to accommodate for the estimated 25% proportion of participants achieving a sustained reduction in cigarette consumption of at least 90% in arm B (as detailed in the Statistical Considerations section). Smokers in the control group (arm A) will receive standard care, inclusive of cessation counseling (ie, VBA) at each study visit. Smokers in the intervention group (arm B) will have the option to try and choose a preferred C-F NA (ECs and HTPs) from a given pool of popular options present in the respective markets and will also receive VBA.

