#### Statistical Analyses

Statistical methods used in the analysis of this study will include descriptive statistics with the descriptive presentation of the total sample value, mean, SD, median, minimum, maximum, and 95% CIs for (pseudo) continuous data and categorical data. Further evaluations will be summarized in tables by counts and percentage of scores.

Statistical methods for primary study end points will include the following: the Shapiro-Wilk test of normality on calculated values (in case of normal distribution, a 2-sided independent *t* test and in case of nonnormal distribution: a 2-sided Mann-Whitney *U* test) and a linear mixed model with the random factors “center” and “study arms by center.”

Designated as study arm C, the never-smoker group will establish a baseline reference for the oral health parameters. This group is anticipated to provide insights into the underlying changes in the primary study end point (MGI) that may emerge over time in individuals who have never smoked.

Statistical methods for secondary study end points will include the following: for comparisons of each study arm for parameters such as MGI assessment, plaque imaging, dental shade quantitation, tooth stains scores, and oral health–related quality of life questionnaires, the Shapiro-Wilk test of normality on calculated values (in case of normal distribution, a 2-sided independent *t* test and in case of nonnormal distribution: a 2-sided Mann-Whitney *U* test); for comparisons of each assessment time for parameters such as MGI assessment, plaque imaging, dental shade quantitation, tooth stains scores, and oral health–related quality of life questionnaires, the Shapiro-Wilk test of normality on calculated values (in case of normal distribution, a 2-sided independent *t* test and in case of nonnormal distribution: a 2-sided Mann-Whitney *U* test); accounting for missing, unused, and spurious data.

If only one value of the parameter MGI is missing after day 1, the last available observation will be carried forward. The analysis will be performed on the substituted data. For secondary parameters, no replacement of missing values will be applied.

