Fourth, maximizing the magnitude of observable changes at the study end points is critically important. Given that several factors (including duration of smoking exposure, variations in oral hygiene practices, type of diet, and level of alcohol consumption) can significantly affect assessments of gum health and dental esthetics, we reduced baseline variability by using data obtained after the visit during which scaling and polishing was carried out. By removing dental plaque, calculus, and stains, we provide all study participants with the best possible oral health status (gum health and teeth appearance) at the beginning of the study. Considering that a 14-day interval is generally required to allow gingival restoration from tissue trauma caused by scaling and polishing [51], measurements that will be considered for this normalized baseline will be obtained 14 days after scaling and polishing. Any progressive change in gum health or tooth appearance will be compared with the reference data of this baseline. In addition to the inclusion of a full scale and polish at the beginning of the study in an attempt to maximize the magnitude of observable changes of study end points, it is also important to consider that the length of the study is adequate and that the study population will have to be one that allows the possibility of measuring such a change. Although the long-term impact of smoking and smoking cessation on gingival health and tooth appearance has never been investigated in a prospective trial, the planned 18 months duration of the study is deemed to be adequate for the detection of significant changes in study end points. Chronic periodontal disease is common in smokers and is an irreversible condition that may stabilize with active treatment [52]; however, it is unlikely to improve with the simple measure of smoking cessation alone. Therefore, participants with periodontitis will be excluded and only participants with mild to moderate gingivitis will be recruited, as they are more likely to show measurable changes in study end points with continuing to smoke, smoking cessation, or the use of C-F NA.

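### Carrying forward a single missing MGI value can bias the month-18 contrast, leaves earlier dropouts with no stated route into it, and is dated from a day that has no visit

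*Protocol article*

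**What the plan says.** The Statistical Analyses section of the protocol article gives one rule for missing MGI: "If only one value of the parameter MGI is missing after day 1, the last available observation will be carried forward". It continues: "The analysis will be performed on the substituted data". The Abstract repeats the rule as "Only if one value of the parameter MGI is missing after day 1, the last available observation will be carried forward". For the other end points, "For secondary parameters, no replacement of missing values will be applied". The article states no rule for two or more missing MGI values.

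The primary end point is the change in MGI from baseline to 18 months, arm A against arm B (Primary End Points). The named analyses are a two-sided t test or Mann-Whitney U test, chosen by a normality test, and a linear mixed model whose only named random factors are centre and arm by centre.

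MGI is scored at day 0 (V0), day 14 (V1), and days 90, 180, 360 and 540 (V2 to V5). Baseline is V1: "day 14—baseline visit (visit 1"). The V0 score precedes cleaning: "All participants will undergo a series of measurements (Tables 1-3) followed by dental scaling and polishing procedures to remove calculus, plaque, and stain". The Discussion explains that the post-scaling score was chosen to reduce baseline variability, and adds: "Any progressive change in gum health or tooth appearance will be compared with the reference data of this baseline".

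**The concern.** The rule raises three problems.

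- **A missing last visit.** Someone who misses only V5 has the V4 score entered as the month-18 score. If MGI is still moving after month 12, the value is wrong on average. If more such values arise in one arm, the error does not cancel. The tests also treat the guess as data, so the standard error is too small.
- **Earlier dropouts.** Someone who leaves before V4 misses at least V4 and V5, so the rule does not apply. The two-group tests need a month-18 change. The mixed model, as described, has no participant or visit effect that would bring in earlier scores. These participants seem to be lost from the primary comparison although their V2 or V3 scores may exist.
- **The starting day.** The schedule has no day-1 visit. Taken literally, a missing day-14 baseline lies after day 1, and the last available score is then the pre-scaling V0 score. That would undo the purpose of the post-scaling baseline.

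The trial is open-label and lasts 18 months. Reasons for withdrawal include nonattendance, uncooperative behaviour and protocol deviations (Study Withdrawal), so loss related to arm or outcome is plausible.

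**Working it through.** The plan gives no figure for the effect of this rule. Its planning inputs do reproduce: a difference of 0.10, SD 0.21, one-sided 5% and 90% power give 77 per group by the exact t calculation. The other inputs used here are 20% dropout and 92 + 368 = 460 randomised (Sample Size Calculation), and the visit days (Study Design).

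**1. Share of the change present at V4.** Assume change is linear from day 14 to day 540. Then (360 − 14)/(540 − 14) = 346/526 = 0.658. A carried V4 score omits 180/526 = 0.342 of the change.

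**2. Who is imputed.** Assume 20% dropout by day 540, a constant withdrawal rate from day 14 and no return. The proportion remaining at day t is S(t) = 0.8^((t − 14)/526).
- S(360) = 0.8^0.658 = 0.8635.
- Leave before V4, no imputed value: 1 − 0.8635 = 13.7%, about 63 of 460.
- Leave between V4 and V5, imputed: 0.8635 − 0.80 = 6.3%, about 29 of 460.
- The rule reaches 6.35/20 = 32% of dropouts.

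**3. Effect on a true difference of 0.100, equal dropout.** Imputed values make up 0.0635/0.8635 = 7.35% of those analysed. The estimate is 0.100 × (1 − 0.0735 × 0.342) = 0.0975 (0.09748 unrounded, so about 0.097).

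**4. Worst case: every dropout attends V4 and misses only V5.**
- 20% in both arms: 0.100 × (1 − 0.20 × 0.342) = 0.093.
- 25% in A and 15% in B, with assumed rises of 0.20 and 0.10: 0.20 × (1 − 0.25 × 0.342) − 0.10 × (1 − 0.15 × 0.342) = 0.1829 − 0.0949 = 0.088. The 25%/15% split and the two rises are assumptions, not figures from the article.

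**5. No true difference, unequal dropout.** Let both arms rise by m, with 10% dropout in A and 30% in B at constant rates. Imputed shares are (0.9^0.658 − 0.9)/0.9^0.658 = 3.5% and (0.7^0.658 − 0.7)/0.7^0.658 = 11.5%. The spurious A − B difference is m × 0.342 × (0.115 − 0.035) ≈ 0.027m, that is 0.003 for m = 0.1 and 0.008 for m = 0.3. Reversing the dropout rates reverses the sign.

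**6. V0 carried into V1.** If V0 exceeds V1 by D and a fraction q of an arm misses only V1, that arm's mean change shifts by −D × q. With D from 0.1 to 0.5 and q from 2% to 10% (both assumed), the shift runs from −0.002 to −0.050, or 2% to 50% of the planned 0.10. It cancels between arms only if D × q is the same in both.

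**The case against.** Several points on the other side carry weight.

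- **Bias is conditional.** The article compares any progressive change with baseline; it does not forecast a trajectory. If MGI levels off by month 12, carrying V4 forward costs little. With equal dropout the illustration shrinks the difference, which is conservative for a superiority claim. This stands: the rule can bias the contrast, the direction is not fixed, and the calculated size is small.
- **Exclusion is inferred.** The article never says that participants with two or more missing scores are left out, and analysis sets may be defined in an analysis plan not shown. This stands as a caution. But the carry-forward rule and the tests are stated here, and none of them uses partial data. Leaving out incomplete cases always loses precision; it causes bias only if the loss is informative.
- **Day 1 may mean visit 1.** That reading removes the baseline problem. The Study Design section and the Discussion both fix baseline as the post-scaling score, and arm B receives its device at V1 (Table 4), so continuing without V1 is unlikely there. No MGI values are given for V0 or V1. This largely stands, but the wording still needs correcting.
- **The 20% refers to two years.** At a constant rate over 730 days, dropout by day 540 would be 1 − 0.8^(526/730) = 15%, with 0.8^(346/730) − 0.8^(526/730) = 4.8% imputed. That makes the effect smaller still.

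A reader might also infer that all of the roughly 92 expected dropouts (20% of 460) would be imputed, or that the difference falls to 0.093 or 0.088. The rule does not support this: it excludes anyone missing two or more values, so those figures need every dropout to miss V5 alone.

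**Conclusion.** The concern holds in a limited form. The carry-forward rule is a stated choice for the primary end point, not a detail left to another document, and it is weak. It enters day-360 scores as observed day-540 scores, and it offers nothing for those who leave earlier.

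Under constant withdrawal to 20% and linear divergence to 0.10, about 6% of participants are imputed, about 14% get no imputed value, and the estimated difference is about 0.097. The worst cases are 0.093 and 0.088. The larger issue is therefore the apparent loss of about two thirds of dropouts from the comparison, whose effect depends on why they leave and cannot be sized from the article.

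It would go too far to say that a pre-scaling score will be carried into the baseline and produce a false fall in MGI. The literal wording allows it, the definition of baseline speaks against it, and whether MGI would fall depends on values that the article does not give. This part is a wording defect to correct.

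**What to change.** Make these changes before unblinding:

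- Replace carry-forward as the primary approach. Estimate the month-18 A − B contrast from a repeated-measures mixed model on all observed MGI at V2 to V5, with baseline MGI, centre, visit, arm by visit and within-participant correlation. Include every randomised participant with any post-baseline value.
- Define the missing-data rule by visit rather than by day. State that V0 is never carried into V1, and say how a participant without V1 enters the model, since the baseline adjustment needs that score.
- Keep carry-forward only as a sensitivity analysis, and add one for data not missing at random.

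No new data are needed, because MGI is already scored at each visit. The cost is more than a change of wording. The mixed model now described has no visit or participant effect, so this is a new primary model with more specification and programming. It also relies on data being missing at random, which open-label withdrawal may violate; the added sensitivity analysis is there to test that.

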Throughout the study, monitoring of cigarette consumption, daily C-F NA use, and oral hygiene routine will be carried out regularly using the tracker app and personal diaries. Monitoring of cigarette consumption and daily C-F NA use will also be achieved by asking participants in arm B to return all empty, partly used, and unused consumables (tobacco sticks, EC cartridges, and e-liquid refill bottles) at each study visit. The tracker app will also identify any protocol violations, collect adverse events (AEs), and send reminders (eg, next scheduled appointment, study restrictions, and instructions) throughout the study duration. The use of a dedicated tracker app adds an innovative element to continuously collect data and enhances adherence to the study protocol.

Before each study visit (visits 1-5), all participants will be required to refrain from scaling and polishing procedures, avoid modifying their habitual oral hygiene (eg, mouthwash, mouth rinse, and interdental floss), refrain from flossing for at least 72 hours before each study visit, refrain from mouth rinsing for at least 24 hours before each study visit, refrain from tooth brushing for at least 2 hours before each study visit, refrain from eating and drinking (except water) for at least 2 hours before each visit, and abstain from smoking for 2 hours before each visit. This is to minimize any potential interference with study outcomes and to maintain consistency in data collection. Throughout the study, any modifications in the oral hygiene routine of participants will be recorded using the tracker app.

A detailed description of the measurements that will be specifically performed at each trial visit is provided in Multimedia Appendix 1.

**Table 1 table1:** Study schedule of procedures (control group—arm A).

Procedure	Screening	Enrollment (V0); day 0	Baseline (V1); day 14±3	Week 12 (V2); day 90±5	Week 24 (V3), day 180±7	Week 52 (V4); day 360±7	Week 76 (V5); day 540±7
Eligibility criteria check	✓	✓					
Medical and oral health Hx^a^	✓						
Smoking Hx	✓						
Intention to quit smoking	✓						
Smoking cessation advice	✓	✓	✓	✓	✓	✓	✓
Cigarette consumption	✓	✓	✓	✓	✓	✓	✓
Exhaled CO^b^	✓	✓	✓	✓	✓	✓	✓
Interest to switch to C-F NA^c^	✓						
Informed consent		✓					
FTND^d^		✓					
Oral hygiene check	✓	✓	✓	✓	✓	✓	✓
Periodontal examination	✓						
Scaling and polishing		✓					✓
Randomization		✓					
Tracker app installation		✓					
BP^e^, HR^f^, weight, height, and BMI		✓	✓	✓	✓	✓	✓

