A generalized linear regression model will be used to adjust for all identified confounders. To identify possible predictors of primary and secondary study end points, a regression model will be estimated in which each study end point will be entered as the dependent variable. Possible predictors will be entered into the model as independent variables (including study group; age; gender; cigarette consumption; combustion-free nicotine delivery systems use; and frequency of personal oral hygiene, eg, tooth brushing, mouth washing, and dental flossing frequency) to assess the interactions. Following the results obtained from each regression model, comparisons between and within study groups will be performed using analysis of covariance adjusted for age, gender, and frequency of personal oral hygiene followed by the Tukey post hoc comparison test.

The goal of our study is to help smokers abstain from cigarette smoking to assess changes in oral health regardless of the product used. This study is not designed to compare the efficacy between HTPs and ECs in terms of smoking cessation. Nonetheless, we will consider a secondary analysis that takes into account the potential different impact of HTPs versus ECs in terms of oral health outcomes.

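### The regression said to adjust for confounders puts product use and undated cigarette consumption beside study group, so its arm coefficient is not the effect of allocation; the ANCOVA leaves hygiene frequency undated and omits baseline MGI and centre

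*Protocol article*

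**What the plan says.** The last part of Statistical Analyses in the protocol article describes three steps.

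- A purpose: "A generalized linear regression model will be used to adjust for all identified confounders".
- A model for each end point: "To identify possible predictors of primary and secondary study end points, a regression model will be estimated". Its variables are given as follows: "Possible predictors will be entered into the model as independent variables (including study group; age; gender; cigarette consumption; combustion-free nicotine delivery systems use". Oral hygiene frequency completes the list, and the stated use is to assess interactions.
- A group comparison that follows the regression results: "comparisons between and within study groups will be performed using analysis of covariance adjusted for age, gender, and frequency of personal oral hygiene", then Tukey tests.

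The primary comparison is described earlier in the same section and is separate: "in case of normal distribution, a 2-sided independent *t* test and in case of nonnormal distribution: a 2-sided Mann-Whitney *U* test", together with "a linear mixed model with the random factors" centre and study arm by centre. No behavioural covariate is listed there.

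On timing, Study Design says that "monitoring of cigarette consumption, daily C-F NA use, and oral hygiene routine will be carried out regularly using the tracker app" and diaries throughout the study. Tables 1 and 2 also schedule cigarette consumption and an oral hygiene check at screening and at enrolment (V0).

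**The concern.** A confounder of a randomised comparison would have to precede allocation. Product use does not: regular prior use of such products is an exclusion criterion, only arm B is supplied, and Table 4 places supply from V1. The variable is close to a relabelling of arm. On-study cigarette consumption is a consequence of allocation and is also the mechanism under test. The Discussion says the trial tests whether avoiding cigarette smoke toxicants improves the gingival response.

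A model holding both fixed asks what the arm does apart from changing smoking and product use. That is not the trial's question. A reader could be shown an arm coefficient near zero, described as adjusted for all confounders, beside a favourable unadjusted difference, with nothing in the article saying which to believe.

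The ANCOVA is a milder case. Hygiene frequency is followed on study in participants who know their allocation, so an on-study value could also respond to arm.

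**Working it through.** **Which model contains what** (all from Statistical Analyses)

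| Analysis | Cigarette consumption | Product use | Hygiene frequency | Baseline MGI | Centre |
|---|---|---|---|---|---|
| Primary t test or Mann-Whitney test | no | no | no | through the change score only | no |
| Linear mixed model | not listed | not listed | not listed | not listed | random |
| Predictor regression | yes, no time point | yes | yes, no time point | not listed (open list) | not listed (open list) |
| ANCOVA and Tukey | no | no | yes, no time point | not listed | not listed |

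**The plan's own figure.** Inputs from Sample Size Calculation: difference 0.10, SD 0.21, 1-sided 5%, power 90%. The normal approximation is n = 2(SD/difference)²(z₀.₉₅ + z₀.₉₀)² = 2 × 4.41 × (1.645 + 1.282)² ≈ 75.5, so 76. The exact noncentral t calculation gives 77, as stated. This figure is not affected. It supplies the scale for the next step.

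**Simulation of the arm coefficient.** There were 1,500 runs per scenario, with 77 in arm A, 4 × 77 = 308 in arm B, and residual SD 0.21. Assumptions not in the documents:

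- 5% of arm A also reduce by at least 90%.
- MGI change depends on arm only through cigarette reduction R, as -0.1 × R/0.95.
- Product use tracks R.
- Hygiene is unrelated to arm.

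The expected total effect is -(0.1/0.95) × (mean R in B - mean R in A), with mean R in A = 0.05 × 0.95 = 0.0475. For example, if 25% of B reduce by 90-100% and the rest by 0-80%, mean R in B = 0.25 × 0.95 + 0.75 × 0.40 = 0.5375. The effect is then -0.1053 × 0.49 = -0.052, against -0.051 simulated.

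| Arm B behaviour | Unadjusted | ANCOVA covariates | Plus cigarettes and product use | Rejection (2-sided 5%): ANCOVA set, then with both added |
|---|---|---|---|---|
| 25% reduce ≥90%, rest none | -0.020 | -0.020 | 0.000 | 10%, 4% |
| 25% reduce ≥90%, rest 0-80% | -0.051 | -0.051 | 0.000 | 46%, 5% |
| 50% reduce ≥90%, rest 0-50% | -0.059 | -0.059 | -0.001 | 57%, 4% |
| 95% reduce ≥90% | -0.090 | -0.090 | -0.001 | 92%, 5% |

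The 25% share comes from Sample Size Calculation; the other shares are assumed. In the last row the empirical SD of the coefficient also rises from 0.027 to 0.056, because the added variables are nearly collinear with arm.

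**Range for partial mediation.** In a linear model without unmeasured common causes of behaviour and MGI, the adjusted coefficient is about (1 - m) × total effect, where m is the share carried by the added variables. For a total of -0.051:

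- m = 0.25: 0.75 × -0.051 = -0.038
- m = 0.50: 0.50 × -0.051 = -0.026
- m = 0.75: 0.25 × -0.051 = -0.013
- m = 1: 0

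The documents give no value for m. Common causes of on-study smoking and gingival health would add bias in either direction; that was not simulated. Because hygiene was generated independently of arm, the simulation gives no size for the hygiene point.

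**The case against.** The strongest reply is that the quoted list belongs to a model for finding predictors, and that the group comparison is a later step without cigarette consumption or product use. That is right, and it limits the point. A reader might infer that the adjusted group comparisons remove the effect the trial exists to estimate, or that the fault carries into the ANCOVA because that step follows the regression results. The stated ANCOVA covariates do not support this: with that set the simulated arm difference equals the unadjusted one. The primary test and mixed model are likewise unaffected.

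It can also be said that cigarette consumption may mean the screening or V0 value, which would be a legitimate covariate, and that time points are often left to a SAP. That too is fair; the missing time point alone would not be a finding. Product use has no such reading, and the article itself names it beside study group under the purpose of adjusting for confounders.

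The near-total loss in the simulation follows from assuming full mediation. It illustrates the mechanism and does not forecast the trial.

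Adjusting comparisons with arm C for age, gender and hygiene is reasonable, since never smokers are not randomised. Participants are also asked not to change their hygiene habits, which makes a large arm effect on hygiene less likely. Centre is handled in the mixed model, and the primary end point is already a change score. Omitting baseline MGI and centre from the ANCOVA is therefore a weakness mainly of precision and consistency; it does not invalidate the comparison.

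**Conclusion.** The concern holds for the regression model. With product use, and possibly on-study cigarette consumption, held fixed, its study-group coefficient does not estimate the effect of allocation, and nothing in the article says it will not be read that way. The attenuation depends on the degree of mediation: about half at 50%, and near complete only if smoking reduction carries the whole effect.

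The main estimate is not at risk. For the ANCOVA the conclusion is narrower: hygiene frequency needs a pre-treatment time point, and baseline MGI and centre should be among the covariates. This merits correction before the analysis but does not threaten the primary result.

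**What to change.** 1. In every model whose study-group coefficient is interpreted, allow only pre-treatment covariates. Take cigarettes per day and hygiene frequency from screening or V0, and remove product use and on-study cigarette consumption. V1 behaviour is less suitable because it falls 14 days after open-label allocation.
2. Add baseline MGI and centre to age and gender in the ANCOVA. For arm A against arm B, baseline MGI can be the V1 value, provided scoring precedes product supply at that visit, or the V0 value. State which.
3. Label any model containing on-study cigarette consumption or product use as an exploratory exposure-response analysis, with no claim about the arm effect, and reword the sentence on confounders to match.

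The cost is a few lines in the analysis plan, settled before outcome data are analysed by arm. MGI, cigarette consumption and an oral hygiene check are already scheduled at V0 for all arms. The one thing to confirm is that the hygiene check records frequency, which the article does not spell out. The exploratory information in the behaviour models is kept.
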